# Integrated telehealth intervention to reduce chronic pain and unhealthy drinking among people living with HIV: protocol for a randomized controlled trial

**DOI:** 10.1186/s13722-024-00493-3

**Published:** 2024-09-05

**Keywords:** Alcohol, Chronic pain, HIV, Telehealth, Ecological momentary assessment

## Abstract

**Background:**

Unhealthy alcohol use represents a significant risk for morbidity and mortality among people living with HIV (PLWH), in part through its impact on HIV management. Chronic pain, a common comorbidity, exacerbates suboptimal engagement in the HIV care continuum and has reciprocal detrimental effects on alcohol outcomes. There are no integrated, accessible approaches that address these comorbid conditions among PLWH to date. This paper describes a research study protocol of an integrated telehealth intervention to reduce unhealthy drinking and chronic pain among PLWH (Motivational and Cognitive-Behavioral Management for Alcohol and Pain [INTV]).

**Methods:**

Two-hundred and fifty PLWH with unhealthy drinking and chronic pain will be recruited nationally via online advertisement. Informed consent and baseline assessments occur remotely, followed by 15 days of ecological momentary assessment to assess alcohol use, chronic pain, functioning, and mechanisms of behavior change. Next, participants will be randomized to either the INTV or Control (CTL) condition. Individuals in both conditions will meet with a health counselor through videoconferencing following randomization, and those in the INTV condition will receive 6 additional sessions. At 3- and 6-months post-baseline, participants will complete outcome assessments. It is hypothesized that the INTV condition will result in reduced unhealthy alcohol use and pain ratings compared to the CTL condition.

**Conclusion:**

This protocol paper describes a randomized controlled trial which tests the efficacy of a novel, integrated telehealth approach to reduce unhealthy alcohol use and chronic pain for PLWH, two common comorbid conditions that influence the HIV treatment cascade.

**ClinicalTrials.gov identifier:**

NCT05503173.

## Introduction

Unhealthy alcohol use represents a significant risk for morbidity and mortality among people living with HIV (PLWH) and is estimated to occur among 10 to 38% of patients depending on sample characteristics [1–3]. Unhealthy alcohol use refers to the consumption of alcohol that places individuals at risk for negative health outcomes and ranges from consumption of amounts that represent increased risk through severe alcohol use disorders [4]. Heavy drinking, defined as consuming more than 14 standard drinks per week or more than 4 standard drinks on any day for men and more than 7 standard drinks per week or more than 3 standard drinks on any day for women, is commonly identified as an amount that represents risk to health [5]. However, the amount of alcohol associated with mortality and physiologic injury may be lower among PLWH [6]. Both suboptimal viral suppression and faster HIV disease progression are associated with unhealthy alcohol use, [5, 7] which may be mediated directly through biological mechanisms (e.g., inflammatory processes) or indirectly through engagement in a variety of behaviors including poor linkage to care, missed healthcare appointments, suboptimal or non-adherence to antiretroviral therapy (ART), unprotected sexual activity, and injection drug use [1, 8–11]. Unhealthy alcohol use is also associated with the likelihood and severity of several comorbid conditions among PLWH impacting mental and physical health [12, 13]. 

Common comorbidities among PLWH, including chronic pain, exacerbate unhealthy drinking and its impact on HIV outcomes. Among patients presenting to HIV clinics, 35–50% experience chronic pain [12, 14]. Moreover, as the population of PLWH ages, pain has become more common, originating as a complication of HIV itself (e.g., neuropathy; [15]) and from common age-related conditions (e.g., arthritis). Not only is chronic pain associated with more severe HIV-related symptoms and reduced engagement with HIV care [16], but it also increases negative alcohol-related consequences among patients meeting criteria for unhealthy drinking across medical settings [17, 18]. Pain influences alcohol use through a variety of pathways (e.g., alcohol use to cope with pain; [19]) and compounds the impact of unhealthy alcohol use on HIV-related health outcomes such as frailty and poor physical functioning [20–22]. Given that pain commonly co-occurs with unhealthy drinking among PLWH, that they have reciprocal influences on one another [17], they impact mental and physical functioning, and they have additive effects on HIV-disease progression [14, 23], it is critical to develop and test approaches to address these concerns among this population.

While pharmacological treatments are available for pain, they are often inadequate for long-term pain management and complicated by comorbid conditions, including substance use history [24]. It is therefore often necessary to identify effective non-pharmacological treatments to adequately manage pain over time. Efforts to address unhealthy drinking among PLWH present other challenges, as the majority of individuals are unaware of the health risks associated with their alcohol use and do not seek alcohol treatment resources [25]. Furthermore, there are few alcohol services routinely offered in HIV care settings [26]. The need for multiple in-person clinic visits compounds challenges related to access, utilization, and adherence to behavioral treatments for unhealthy drinking and pain. Providing alternative intervention modalities that do not require repeated in-person medical visits is critical for reducing patient burden, increasing access to care, and improving treatment efficacy.

This paper describes a study protocol for a randomized controlled trial (RCT) that aims to test the efficacy of an integrated telehealth intervention for reducing unhealthy drinking and chronic pain among PLWH that may be implemented in a fully remote context. The secondary aims are to examine the moderators of the Motivational and Cognitive-Behavioral Management for Alcohol and Pain (INTV) effect and the mediational pathways of the INTV effect. Baseline interview-administered self-report and ecological momentary assessment (EMA) will be used to identify potential individual difference factors that moderate intervention efficacy. Post-intervention EMA, which provides the advantage of real-time assessment of self-regulatory processes and contextual influences on those processes, will be used to identify potential mediators of the intervention and explore mechanisms of behavior change [27, 28].

## Method

This RCT is a project component of ARCHER (Addressing Related Comorbidities for HIV by Employing Remote technologies), an HIV Center funded by National Institute on Alcohol Abuse and Alcoholism (P01AA029546). The trial is registered on ClinicalTrials.gov (NCT05503173). This study is conducted in compliance with the protocol and applicable regulatory requirements approved by the Boston University Medical Campus/Boston Medical Center Institutional Review Board and Human Research Protection Program.

### Overall design

Participants will be PLWH who engage in unhealthy drinking and experience moderate or greater chronic pain recruited nationally via online advertisement. Those who are eligible based on an initial set of online prescreening questions will be contacted by study staff for a more comprehensive phone screening. Those who remain eligible based on the more extensive screening will be scheduled for baseline assessment during which they will provide informed consent, confirm HIV diagnosis, and complete baseline questionnaires administered in an interview format. Staff will also orient participants to the EMA procedures whereby they will complete 5 surveys per day for the following 15 days. After EMA data collection, participants will undergo 1:1 randomization into either the intervention group (INTV) or the control (CTL) group. The INTV condition is a 7-session program designed for weekly delivery through videoconferencing by a health coach. Those in the CTL group meet virtually with the health coach for a single session and be provided with information and resources about alcohol and pain. At three-month outcome assessment, staff will administer questionnaires via interview, prior to another 15 days of EMA data collection. The final study assessment occurs six months after randomization and will include a staff-administered interview and a self-collected blood draw to measure phosphatidylethanol (PEth), a biological marker of alcohol use (see [29]). Participants complete self-collected blood draws at home and with guidance through videoconferencing (Fig. 1).

**Fig. 1 Fig1:**
[figure not shown]
Study flow diagram

### Rationale for study design

The study is designed to test the efficacy of INTV, but has several additional objectives including, (1) the use of a nationally representative sample, (2) implementation of all study procedures remotely, (3) being able to identify potentially important moderators of intervention efficacy, and (4) providing detailed analyses of the processes through which the intervention may impact outcomes. Recruitment through social media will target PLWH across the country in areas defined by the CDC as having high HIV prevalence rates. This fully remote approach reduces participant burden and increases study efficiency. Finally, the study design incorporates the use of EMA. Multilevel modeling allows for an examination of how treatment may change associations between contextual cues (e.g., mood) and outcomes of interest (e.g., drinking, pain) over time. This approach enables fine-grained analysis of how the intervention may impact pain, alcohol use, and their interaction, in addition to providing insight into psychological processes (e.g., self-efficacy) through which these influences may occur. Such information will provide insight into how and for whom the interventions may reduce heavy drinking and pain.

### Study aims and hypotheses

#### Primary aim

This study aims to test the efficacy of INTV for reducing unhealthy drinking and chronic pain among PLWH. The primary alcohol outcomes will be the average number of drinks per week and number of heavy drinking episodes over the past month. The primary pain outcome will be a composite measure of pain intensity and interference (i.e., pain average, interference with enjoyment of life, and interference with general activity) known as the PEG; [30]). Primary analyses will focus on alcohol and pain outcomes assessed at 6-month follow-up. It is hypothesized that those randomized to INTV will show fewer drinks per week, fewer episodes of heavy episodic drinking (primary alcohol outcomes), and lower ratings of pain at the 6-month assessment compared to the those in the CTL group, controlling for corresponding baseline values.

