### Assessments

#### Assessment procedures

Assessments will include interview-administered instruments at baseline, 3 months post-randomization, and 6 months post-randomization. In addition, there will be two 15-day EMA data collection periods (one at baseline and one at 3-months), a treatment satisfaction measure, and a blood draw to test a biological marker of alcohol use, phosphatidylethanol (PEth; [29]) self-administered 6 months-post randomization.

Participants will complete all assessment interviews (baseline, 3-month follow-up, and 6-month follow-up) virtually through a videoconferencing platform or by phone. Interviews will take approximately 90 to 120 min and are each associated with $50 compensation for time and effort.

In addition to research interviews, participants will complete two phases of EMA data collection over 15-day periods. The first 15-day EMA period begins following the baseline interview while the second 15-day EMA period takes place following the 3-month assessment interview. Participants will learn about EMA procedures following the baseline interview, including how to use the EMA iOS or Android mobile application (MetricWire; [36]. Each day during the EMA periods, MetricWire will prompt participants to complete a morning survey and four additional surveys which arrive randomly throughout the day.

Upon completing the 15 days of EMA surveys at the 3-month time point, participants will be notified to complete one final survey on intervention satisfaction and acceptability for which they will be compensated $5. Across all study activities, participants will be able to earn up to $480 over the 6 months. Payments are made via electronic gift certificates.

Finally, at the 6-month outcome assessment interview, participants will be able to earn an additional $25 for completing and sending a self-administered blood sample to the collaborating laboratory [29].

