### Statistical design and analysis

#### Sample size determination

A sample size of 250 (*n* = 125 to each condition) will be randomized. With a conservative estimate of a 20% attrition rate by 6-month follow-up, this sample size gives power (80%) to detect medium effects (Cohen’s d = 0.40) at the 2-tailed significance level (0.05) for INTV versus CTL at 6-month follow-up on both pain and alcohol outcomes. The anticipated effect size is based on the following: (1) meta-analyses of CBT interventions compared to assessment and minimal interventions suggesting medium post-intervention effects on alcohol and pain; [98–100] and (2) results of our pilot study which showed medium-to-large pre-to-post changes (Cohen’s d from 0.79 to 1.0) within participants receiving INTV [95, 96]. Moreover, the availability of repeated measurements (to include a baseline covariate) increases statistical power to detect intervention effects for the analysis.

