#### Primary and secondary analyses

Descriptive statistics will be provided for the baseline characteristics of the full sample and by condition (i.e., INTV vs. CTL). Multiple linear regression analyses will be used to test whether those in the INTV group consume fewer drinks per week, engage in fewer episodes of heavy episodic drinking, and report lower PEG ratings than those in the CTL group at 6-month outcome. Covariates will include age, sex at birth, and corresponding baseline measures of alcohol use and pain. Secondary analyses will examine related outcomes (i.e. alcohol related consequences, pain intensity, pain severity) using a parallel approach. Exploratory analyses will examine INTV effects on outcomes including substance use frequency, depressive symptoms, anxiety symptoms, HIV symptom index scores, HIV risk-taking behaviors, mental functioning, and physical functioning at 6 months using multivariate regression models. For PEth analyses, we will use the lower limit of quantification as a cut-off of > 50 as a measure of unhealthy alcohol use and a cutoff of PEth > 8 ng/ml) as a marker of any alcohol use. Logistic multiple regression with the age and race/ethnicity will be used to examine intervention effects on 6-month PEth outcomes [101]. Secondary aims will be addressed, in part, by using baseline interview measures of readiness-to-change (for alcohol) and baseline GSAB questionnaire ratings of self-efficacy and planning (for both alcohol and pain outcomes). Planned covariates include those described under primary aims and will include baseline values of the questionnaire measure being evaluated. The Condition x Moderator term will be added to the full models to examine interaction effects, which will be followed with simple slopes analyses to determine the direction of effects.

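### The stated primary regression at 6 months makes no use of the month-3 values of the same outcomes, which could weaken its missing-data assumption under the planned 20% attrition

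*Protocol article*

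**What the plan says.** Under Primary aim, the protocol article fixes the time point: "Primary analyses will focus on alcohol and pain outcomes assessed at 6-month follow-up". Primary and secondary analyses then fixes the model: "Multiple linear regression analyses will be used to test whether those in the INTV group consume fewer drinks per week", and the same regression covers heavy drinking episodes and PEG ratings, all at 6 months. The covariates are age, sex at birth and the corresponding baseline measure.

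The same outcomes are also measured in between. Assessment procedures states: "Participants will complete all assessment interviews (baseline, 3-month follow-up, and 6-month follow-up". Table 1 marks the 30-day Timeline Followback and the PEG at baseline, month 3 and month 6.

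Sample size determination allows for loss: "With a conservative estimate of a 20% attrition rate by 6-month follow-up". It mentions repeated measurements as a source of power, but only because they supply a baseline covariate. The article gives the month-3 Timeline Followback and PEG values no role in the primary analysis. It names no analysis set and does not say how missing 6-month values are handled.

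**The concern.** A regression of a single 6-month value can only be fitted to people who have that value. Unless a missing-data method is added, the planned one in five without a 6-month interview contribute nothing, even those who gave the same measures at month 3.

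Such a regression is safe if, given arm and covariates, missingness is unrelated to the 6-month outcome. That condition is sufficient but not necessary: selection that acts alike in both arms can cancel out of the contrast. The worry is selection that differs by arm. INTV offers seven sessions and CTL one, so it is plausible, though not documented, that poor progress affects retention differently in the two arms. Month 3 is the last view of progress before the primary time point, and the named model cannot condition on it. At stake is the size of the reported 6-month effect on all three primary outcomes.

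**Working it through.** **1. The plan's own sample size.** Inputs from Sample size determination: 125 per arm, d = 0.40, two-sided 0.05, 80% power, 20% attrition.

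- n per arm = 2(1.960 + 0.842)² / 0.40² = 98.1, so 99.
- Inflated for loss: 99 / 0.80 = 123.75, so 124 per arm and 248 in total, against the stated 250.
- Power with 125 × 0.80 = 100 per arm: Φ(0.40 × √50 − 1.960) = 0.807; by the noncentral t, 0.804.

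The figure reproduces. It counts 100 analysed per arm, which is consistent with an analysis of those who have 6-month data. Inflation of this kind is routine, so it does not prove that such an analysis is intended.

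**2. Assumptions for the bias check.** The article gives no correlations, drop-out mechanism or timing of loss. Assumed: normal outcomes with SD 1; true effect −0.40 SD at months 3 and 6; correlation of baseline with each follow-up 0.5; month-3 to month-6 correlation 0.5 to 0.7; 20% missing at month 6 in each arm; logistic drop-out slope of 1 per SD. Simulations of 2,000,000 records give the large-sample bias.

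**3. Why there is bias, and how much.** When drop-out depends on the month-3 value,

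bias of the 6-month-only regression ≈ β × δ,

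where β is the slope of the 6-month value on the month-3 value given baseline and arm, and δ is the distortion that drop-out creates in the baseline-adjusted month-3 arm difference among those remaining.

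- β = (r₃₆ − 0.5 × 0.5) / (1 − 0.5²), which is 0.25/0.75 = 0.33 at r₃₆ = 0.5 and 0.45/0.75 = 0.60 at r₃₆ = 0.7.
- Same dependence in both arms: δ ≈ 0, so bias ≈ 0.
- Dependence in INTV only: simulated δ ≈ −0.13, so bias ≈ −0.04 to −0.08.
- Opposite dependence in the two arms: simulated δ ≈ −0.27, so bias ≈ −0.09 to −0.16.

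The directly simulated estimates agree. The second estimate column adds month 3 by sequential regression, which stands in for a likelihood analysis. Ranges run over r₃₆ = 0.5 to 0.7.

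| Drop-out depends on | 6-month-only estimate (truth −0.40) | With month 3, all drop-outs have it | Bias left if half lack month 3 |
|---|---|---|---|
| Month-3 value, equally in both arms | −0.40 | −0.40 | about 0 |
| Month-3 value, INTV only | −0.44 to −0.48 | −0.40 | 0.02 to 0.04 |
| Month-3 value, opposite in the arms | −0.49 to −0.56 | −0.40 | 0.04 to 0.07 |
| Unseen 6-month value, INTV only | −0.53 | −0.52 to −0.49 | 0.11 to 0.13 |

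If all drop-outs lack month 3, the two analyses coincide and nothing is removed. In the last row, with month 3 available for all, bias falls from 0.132 to 0.118 (11% removed) at r₃₆ = 0.5 and from 0.131 to 0.085 (35% removed) at r₃₆ = 0.7.

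The sign follows the assumed direction, in which INTV participants doing badly leave. Reversing that in the INTV-only case gives −0.36 to −0.32, an understated effect.

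**The case against.** The strongest reply is that the article never says it will analyse completers only. It is silent on missing data, and an article commonly leaves that to a full protocol or analysis plan. The named regression could be fitted after multiple imputation that includes month 3. This stands. A reader might infer that the plan commits to a completer analysis, but the documents do not support that. What they support is that the model as named does not use month 3.

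A reader might also infer that 20% attrition will bias the result and that month 3 would largely repair it. Neither follows. Bias is about 0 when the dependence is the same in both arms, and the repair needs drop-outs who attended month 3 and whose leaving it explains. The attrition figure is cumulative to 6 months and says nothing about timing. Seven weekly sessions would finish before month 3, so loss driven by unequal contact may come early and take the month-3 value with it.

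Two further replies are fair. Baseline-adjusted regression at one prespecified time point is an accepted primary analysis, and choosing 6 months is not an error. Nor is the remark about repeated measurements inconsistent with the model: a baseline covariate is what the model uses.

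None of this removes the core. The values are collected anyway, adding them did not increase the bias in any scenario examined, and the target of estimation is unchanged.

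**Conclusion.** The point holds as a recommended improvement to the stated model, not as a demonstrated bias. The primary regression leaves unused the month-3 values of its own outcomes and, run as named, leaves out the planned 20% without 6-month data. Where drop-out depends on month-3 progress differently by arm, the distortion is about 0.04 to 0.16 SD, that is 10% to 40% of the planned 0.40 SD (0.04/0.40 and 0.16/0.40).

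These sizes rest on assumed correlations, an assumed drop-out slope and normal outcomes. They are illustrations on an SD scale, not predictions, and less direct for the drinking counts than for the PEG. The stated sample size is sound and is not affected.

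**What to change.** Keep the 6-month arm contrast as the primary estimate, in all randomised participants as allocated, and obtain it in one of two ways:

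- a likelihood-based repeated-measures model with months 3 and 6 as outcomes, arm by time, baseline value, age and sex at birth as covariates, and an unstructured covariance; or
- the stated regression after multiple imputation, done separately by arm, with the month-3 value in the imputation model.

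Report the 6-month-only regression as a sensitivity analysis. Add a sensitivity analysis for data missing not at random, because month 3 removes little of the bias if loss depends on the unseen 6-month value. Tabulate, by arm, how many of those without 6-month data have month-3 data, since that decides how much is gained. If an analysis plan not shown here already uses month 3, a sentence saying so is enough. Either way, settle this before any unblinded analysis.

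The cost is a change of wording under Primary and secondary analyses and slightly more modelling. Endpoint, visits and sample size stay as they are.
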